## Abstract

**Background:**

Kidney transplantation is the optimal treatment in end stage renal disease but the allograft survival is still hampered by immune reactions against the allograft. This process is driven by the recognition of allogenic antigens presented to T-cells and their unique T-cell receptor (TCR) via the major histocompatibility complex (MHC), which triggers a complex immune response potentially leading to graft injury. Although the immune system and kidney transplantation have been studied extensively, the subtlety of alloreactive immune responses has impeded sensitive detection at an early stage.

Next generation sequencing of the TCR enables us to monitor alloreactive T-cell populations and might thus allow the detection of early rejection events.

**Methods/design:**

This is a prospective cohort study designed to sequentially evaluate the alloreactive T cell repertoire after kidney transplantation. The TCR repertoire of patients who developed biopsy confirmed acute T cell mediated rejection (TCMR) will be compared to patients without rejection.

To track the alloreactive subsets we will perform a mixed lymphocyte reaction between kidney donor and recipient before transplantation and define the alloreactive TCR repertoire by next generation sequencing of the complementary determining region 3 (CDR3) of the T cell receptor beta chain.

After initial clonotype assembly from sequencing reads, TCR repertoire diversity and clonal expansion of T cells of kidney transplant recipients in periphery and kidney biopsy will be analyzed for changes after transplantation, during, prior or after a rejection.

The goal of this study is to describe changes of overall T cell repertoire diversity, clonality in kidney transplant recipients, define and track alloreactive T cells in the posttransplant course and decipher patterns of expanded alloreactive T cells in acute cellular rejection to find an alternative monitoring to invasive and delayed diagnostic procedures.

**Discussion:**

Changes of the T cell repertoire and tracking of alloreactive T cell clones after combined bone marrow and kidney transplant has proven to be of potential use to monitor the donor directed alloresponse. The dynamics of the donor specific T cells in regular kidney transplant recipients in rejection still rests elusive and can give further insights in human alloresponse.

**Trial registration:**

Clinicaltrials.gov: NCT03422224, registered February 5th 2018.

**Electronic supplementary material:**

The online version of this article (10.1186/s12882-019-1541-5) contains supplementary material, which is available to authorized users.

## Background

After the introduction of highly potent immunosuppressive regimens in combination with induction therapy, a significant reduction of acute rejection episodes and an improvement in short term graft survival have been achieved [1, 2]. However, a number of transplanted organs are persistently lost following an acute rejection episode, and long-term graft function and survival following this kind of immunological event poses even greater problems to patient management [3, 4].

Acute cellular rejection with infiltrating CD8+ and CD4+ T lymphocytes play a central role and account for the larger fraction of acute rejection episodes [5]. Lymphocyte infiltrates in the kidney are the leading finding of T cell mediated rejection and therefore the nature of infiltrating lymphocytes in the transplanted kidney is of special interest even more as little is known about the antigen specificity of the T cell receptors and the molecular properties of these infiltrates.

Likewise, T cells play a crucial role in the initiation of antidonor antibody formation and consecutively antibody mediated rejection (ABMR). T helper cells support B cells after encountering their antigen by direct interaction and cytokine production which leads to proliferation, differentiation and affinity maturation of B cells to memory B cells or long-lived plasma cells secreting high-affinity antibodies [6–8].

During early T cell development T cell precursors enter the thymus and differentiate to immature T cells. In the thymus, random recombination of germline-encoded TCR variable (V), diversity (D), and joining (J) gene segments aims for the formation of a functional TCR protein and generation of a highly diverse TCR repertoire [9].

Junctional diversification further increases the combinatorial diversity by trimming gene ends or adding nucleotides between the recombining genes and thereby generating hypervariable complementarity-determining regions (CDR1-CDR3). The complementarity-determining region 3 (CDR3), which is the most variable CDR, spans over the V(D) J junction and forms the primary site of antigen contact [9, 10]. The cells expressing a recombined T cell receptor only survive if self MHC (major histocompatibility complex) and a self-peptide presented by thymic antigen presenting cells is recognized with adequate affinity to transmit a survival signal (positive selection). In a second selection process (negative selection) T cells with an operational TCR but an activation above an affinity- or cross-reactivity threshold are send to apoptosis by a death signal as these cells would be more likely to become activated by self-peptides or by the MHC molecule itself and cause autoimmunity [9].

This complex development of the T cell receptor repertoire and selection process results in the generation of a highly diverse repertoire capable of defending an individual against a variety of pathogens and being ideally tolerant to antigens present in the own body. This leads to a large number of unique TCR rearrangements with in theory over 10^13 unique T cell clonotypes representing the immune repertoire [11–13].

After the generation of the immune repertoire events such as infections, aging or immune modulating therapies cause an alteration which can lead to the expansion or deletion of clones and effect the diversity of the overall repertoire [10, 14, 15].

In solid organ transplantation T cells recognizing a foreign antigen or MHC protein, so called alloreactive T cells, expand and cause a rejection with severe organ damage. Receptor diversity analysis of these alloreactive cells using conventional methods such as PCR-based hybridization methods, flow cytometry of V region usage or TCR spectratyping, is a major technical challenge [16–18]. Additionally, these techniques have limitations regarding their resolution:

Fluorescence activated cell sorting (FACS) is limited by the availability of antibodies against T cell receptor’s Variable, Diversity and Joining (VDJ) elements and PCR-based length analysis by spectratyping does not allow to discriminate between clones with identical CDR3 lengths [19, 20].

With the development and technical progress of next-generation sequencing (NGS) technologies it is now feasible to sequence millions of receptor clones simultaneously, which provides a much more detailed and precise picture of the immune repertoire [11, 21, 22]. It is possible to obtain several million sequences per sequencing run and only recently the focus has been put on receptor sequencing of the alloreactive lymphocyte population and the changes in abundancy of these clones and repertoire diversity over time [23].

Two studies of TCR repertoire analysis based on NGS data were published in 2009 using two different experimental designs [11, 21]. These designs differ in the starting material used being either genomic DNA (gDNA) or messenger RNA/complementary DNA (mRNA/cDNA)-based approaches [24, 25]. Both strategies have advantages but also shortcomings. Using genomic DNA in contrast to mRNA as a starting template has the advantage of superior quantification as every T cell only possesses one functional TCR chain, depicting in theory a more precise overall T cell receptor repertoire. A major downside of using gDNA is the significant multiplex PCR bias introduced by different primer annealing or amplification efficiencies leading to over/underrepresentation or dropout of those elements by non-uniform amplification. This bias is reduced in the mRNA/cDNA approach by using template switch during cDNA library preparation which forms universal primer annealing sites on both ends of the library and can be further counteracted by the introduction of unique molecular identifiers (UMIs). However, the mRNA/cDNA approach is known to be less specific and conclusions on absolute frequencies of cells is more difficult due to unequal mRNA expression levels in cells.

Morris et al. recently used mixed lymphocyte reactions (MLR, incubating donor antigen presenting cells (APCs) with recipient T cells) to select alloreactive T cell clones prior to transplantation. Using high-throughput sequencing data of the CDR3 a unique fingerprint of the donor-reactive T cell repertoire was identified before transplantation and donor reactive T cells were tracked posttransplant in blood samples [26]. Further studies validated this approach in different solid organ settings, as in small bowel transplantation, also analyzing T cell repertoires in tissue biopsies [27, 28].

We aim to apply a similar approach in this project to get a closer insight into the alloreactive lymphocyte population prior to transplantation and follow these populations over time and analyze associations of repertoire diversities with the histomorphological phenotype of T cell mediated rejection in the kidney transplantation setting. Further we would like to decipher patterns of expansion of these clones prior to rejection and decline in graft function to hopefully foresee rejection episodes before graft damage occurs.

## Methods/design

This is a single center prospective cohort trial designed to evaluate the value of T cell receptor repertoire sequencing of T cells in the periphery and in the allograft during a biopsy proven rejection episode compared to absence of histological findings of rejection conducted at the General Hospital of Vienna/Medical University of Vienna, Department of Nephrology.

These alloreactive T cells are defined prior to transplantation via a mixed lymphocyte reaction as shown in previous studies [26, 27].

Fifteen patients with histological proven acute T cell mediated rejection will be compared to 15 patients without histopathological signs of alloimmune response in time matched for-cause biopsies. Only recipients of donor organs evaluated and accepted by the local transplant team in Vienna will be included due to lack of availability of donor peripheral blood mononuclear cells (PBMCs) of donors evaluated by Eurotransplant, an Europe-wide program allocating and exchanging deceased donor organs across-borders [29]. The proposed duration of the trial is 36 months. The sample size of 15 patients experiencing an acute T cell mediated rejection and an accrual phase of 24 months was calculated based on historic data from our center. The study protocol and informed consent were designed following the “Standard Protocol Items: Recommendations for Interventional Trials (SPIRIT) 2013 statement” guidelines and the standards of the world health organization research ethics review committee (Additional files 1 and 2) [30, 31].

### Outcome parameters

Expansion or deletion of the pre-transplant defined alloreactive T cell repertoire against the allograft during acute T cell mediated rejection will be compared to patients without biopsy proven rejection. Further analysis of local T cell expansion in the allograft during a rejection episode will be performed via RNA extraction of the frozen biopsy. Additionally an analysis will concentrate on T cell clonality analysis and repertoire diversity of patients over time and of rejecting and non-rejecting individuals.

### Sample collection

For our analysis we will include a minimum of 150 kidney transplant recipients with a for-cause biopsy after transplantation that were enrolled prospectively between february 2018 and february 2020. A medical doctor obtained informed consent of eligible recipients prior to transplantation and recipient and donor PBMCs will be stored at time of transplantation. Only recipients of donors evaluated by the local transplant coordinators will be included in this study due to availability of donor PBMCs. Additionally, surveillance biopsies will be performed at 3 and 12 months and tissue samples as well as PBMCs will be stored in liquid nitrogen and − 80 °C (Fig. 1). De-identification of included patient samples is performed before sample processing by a study specific patient identifier.

**Fig. 1 Fig1:**
[figure not shown]
Study Flowchart. All eligible patients receiving a kidney transplant from donors evaluated at our center will be included and TCR repertoire of total PBMCs and alloreactive T cells will be analyzed. TCR repertoire in the periphery and in biopsies will be assessed at surveillance biopsies and TCMR. DSA: donor reactive antibodies, TCR: T cell receptor, PBMC: peripheral blood mononuclear cells, KTX: kidney transplant, TCMR: T cell mediated rejection

Including 15 samples per group (Rejectors, non-rejectors) our study has 80% power to detect a minimum difference of 0.106 in the mean proportion of alloreactive clones in the posttransplant repertoire of patients from the two groups assuming a standard deviation of 0.1 each. This calculation was performed using Power and Sample Size Version 3.0 (Fig. 2) [32].

**Fig. 2 Fig2:**
[figure not shown]
Detectable effect size versus sample size. Depicted is the relationship between number of samples in the study and minimal detectable difference in population means for standard deviations of 0.05 (red), 0.1 (blue) and 0.15 (pink). SD: Standard deviation

### Inclusion and exclusion criteria

Inclusion criteria for this study are: (1) Kidney transplant recipient, (2) age ≥ 18 years, (3) donor evaluation by the local transplant coordinators and (3) written informed consent. Exclusion criteria for this study are: (1) Donor evaluation by Eurotransplant or (2) lymphodepletional induction therapy.

### Blood samples

At time of transplantation and at time of biopsies as well as 3 and 12 months after transplantation, blood samples will be collected as part of the routine blood draw at the follow up at the outpatient clinic (Table 1). PBMC isolation will be carried out as described.

**Table 1 Tab1:** Schematic diagram of the patient’s timeline (adjusted from SPIRIT guidelines for trial protocols)

Timepoint	Study period				
	Enrolment	Biopsy			Close-out
	Transplantation	For cause	M3	M12	M24
Enrolment:					
Eligibility screen	X				
Informed consent	X				
Interventions:					
PBMC collection	X	X	X	X	
Kidney Biopsy		X	X	X	
Assessments:					
TCR repertoire sequencing of unstimulated PBMCs	X	X	X	X	
TCR sequencing of Alloreactive T cells after MLR	X				
Phenotypic analysis of peripheral T cell populations	X	X	X	X	

*M3* Month 3, *M12* Month 12, *MLR* Mixed lymphocyte reaction, *TCR* T cell receptor, *PBMC* Peripheral blood mononuclear cells

### PBMCs isolation

PBMCs of donors evaluated by our transplant center at the Medical University of Vienna will be isolated via density gradient from whole blood which will be sent along with the renal allograft at transplantation. Recipient PBMCs will be isolated out of whole blood via density gradient at time of transplantation, as described previously [26, 27].

After isolation cells will be stored in liquid nitrogen and − 80 °C for future analysis.

### Tissue samples

#### Surveillance biopsies

At 3 and 12 months surveillance biopsies are performed at our transplant center for patients included in the study with informed consent prior to transplantation and tissue as well as blood samples will be stored.

All biopsies will be evaluated on standard formalin fixed paraffin-embedded (FFPE) sections at the Department of Pathology as part of the clinical routine. Histological slides from FFPE tissue will be made and will be used for routine staining (Hematoxylin-Eosin, Acid Fuchsin Orange G (AFOG), Periodic acid Schiff, Methenamine) and immunohistochemistry. Histopathology scoring will be performed according to BANFF 2017 [33].

A second core will be stored at − 80 °C (in tissue plus OCT compound) until DNA and RNA will be extracted for further analysis (see below).

#### For-cause biopsies

For-cause biopsies are performed routinely in patients with delayed or deteriorating graft function with a low diagnostic threshold to guide and optimize clinical decision-making. The evaluation and biopsy collection will be performed as mentioned above.

### In vitro expansion of donor-specific alloreactive T cell lymphocytes

The protocol of in vitro expansion of donor-specific T cell lymphocytes will be performed as described previously [26]. In short, we will label donor cells with BD HorizonTM Violet Proliferation Dye 450 (VPD-450 catalog # 562158) and recipient cells with carboxyfluorescein succinimidyl ester (CFSE) according to the manufacturer’s protocol prior to resuspension in MLR medium (AIM-V supplemented with 5% AB heat- inactivated human serum, 0.01 M HEPES, and 50 μM 2-ME and 1% Pen/Strep) at a concentration of 2 × 10^6^ cells/mL. Donor cells will additionally be irradiated at 35 Gray [27].

#### Preparation of CFSE-labeled responder cells

After thawing cryopreserved recipient PBMCs will be labeled with carboxyfluorescein succinimidyl ester (CFSE). Subsequently cells will be washed twice, resuspended in MLR medium at 2 × 10^6^ cells/mL.

MLR will be performed by plating 2 × 10^5^ CFSE-labeled transplant responder cells and 2 × 10^5 VPD-labeled irradiated stimulator cells will be plated in each well of a 96-well plate (total well volume 200 μl). MLR cultures will be incubated at 37 °C for 6 days. After incubation, the different dyes will allow us to differentiate between the cells of interest (CFSE- labeled recipient cells) and the unessential cells (VPD-labeled donor cells) [27].

### Fluorescence activated cell sorting (FACS)

Cells will be harvested from the 6 day MLR culture from the 96 well plate, washed with FACS Buffer and counted. Unstimulated PBMCs will be thawed, washed twice with media and PBS, resuspended in FACS buffer and counted [26, 27]. Subsequently the cells will be resuspended in FACS buffer, blocked for 30 min with blocking buffer (10% human serum, 1% BSA) stained for 30 min with fluorochrome-conjugated anti-CD3, anti-CD4, anti-CD8, anti-CD25, anti-CD127, anti-CD45RA and anti-CCR7. Sorting will be done on a FACS Aria II high speed cell sorter. We will isolate two populations after MLR (CFSE low CD4/CD8) and three discrete cell populations for unstimulated PBMCs (CD4, CD8, Treg). Phenotypic analysis of the unstimulated PBMCs pre-and posttransplant includes the following markers:

T helper cells (CD3+, CD4+, CD8-), cytotoxic T cells (CD3+, CD4-, CD8+), Treg cells (CD4+, CD25+++, CD127-, FOX-P3+), central memory cells (CD4/CD8, CD45RA-, CCR7+), effector memory cells (CD4/CD8, CD45RA-, CCR7-) [27, 34]. The sorting of T cell populations is followed by RNA isolation and library preparation for TCR sequencing.

### T cell receptor repertoire sequencing

#### RNA isolation

RNA isolation is done following the original Trizol protocol (Invitrogen, Carlsbad, CA).

### Bioinformatics

A computational workflow for the evaluation of results from NGS based analysis of T cell receptor repertoires will be established. The workflow will cover all aspects of data quality evaluation, demultiplexing of samples and the determination of clonality and diversity (Fig. 3).

**Fig. 3 Fig3:**
[figure not shown]
Bioinformatic Flowchart. A pipeline for the analysis of T cell repertoires. A: First, barcode analysis is done as well as separating the sequences belonging to the different individuals (B). C: Reads that cannot be assigned to a specific individual are stored in a separate FASTQ file for later investigation regarding the origin of these sequences. D: Adapters and barcodes from sequences are trimmed. During this step the UMIs are determined and stored in a separate file (D1). E: Afterwards the sequences are clustered with respect to their reference genes and UMIs. F/G: Clonotypes are assembled and clonality, diversity and repertoire overlap analysis is performed

FastQC will be employed for quality control of raw sequencing data. The quality of each run will be further checked by analyzing the frequency of sample barcodes, their position in the reads, as well as the recovery of phiX. Only reads passing the initial quality control will be analyzed further. Sequences assigned to the individuals characterized by unique nucleotide barcodes are identified and separated.

In preparation for determining the immunological interesting regions (especially the V(D) J regions), the appendages will be trimmed to remove barcodes and any adapters. In the same step the UMIs will be extracted and stored separately for subsequent use during reference gene clustering. Remaining sequences which either miss barcodes or have invalid barcodes will be collected for further analysis of the origin of these sequences.

After preprocessing V(D) J region containing reads will be subjected to reference gene clustering. Therefore, all reads will be aligned to T cell receptor reference sequences, using *Bowtie2*, a tool for aligning sequencing reads to reference genes [36]. Subsequently, reads aligned to the same position in a reference sequence and sharing an UMI will be collapsed into a single read.

Finally, ImmunExplorer will be used to perform clonotype assembly based on the reference gene clustered sequences with MiXCR and to carry out clonality, diversity and repertoire overlap analysis [37, 38].

### Statistical methods

After identification of alloreactive T cell clones prior to transplantation-via one way MLR- the proportion of alloreactive clones in the posttransplant repertoire of rejectors and non-rejectors will be compared by means of t-test.

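### The outcome is expansion or deletion of alloreactive clones, but the only stated test and its power statement compare post-transplant levels without the day-0 value

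*Protocol article*

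**What the plan says.** The Protocol article, Outcome parameters, names what is compared between rejectors and patients without biopsy-proven rejection: "Expansion or deletion of the pre-transplant defined alloreactive T cell repertoire against the allograft during acute T cell mediated rejection will be compared". The Discussion uses expansion in the same sense, relative to the baseline repertoire.

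Statistical methods is a single sentence. After the clones have been identified by the pre-transplant mixed lymphocyte reaction (MLR), "the proportion of alloreactive clones in the posttransplant repertoire of rejectors and non-rejectors will be compared by means of t-test". No other test is named.

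The power statement under Sample collection uses the same variable. With 15 samples per group it claims "80% power to detect a minimum difference of 0.106 in the mean proportion of alloreactive clones in the posttransplant repertoire", "assuming a standard deviation of 0.1 each".

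Table 1 (Blood samples) has a row for "TCR repertoire sequencing of unstimulated PBMCs" that is marked at transplantation, at the for-cause biopsy and at months 3 and 12. Methods/design forms the groups by histology: 15 patients with T cell mediated rejection and 15 without signs of alloimmune response, matched on biopsy time.

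**The concern.** Expansion and deletion need a starting value. In the stated test the pre-transplant MLR only decides which clones are counted. How common those clones already were before transplantation plays no part.

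The groups are defined by outcome, and the only matching mentioned is on biopsy time, so nothing makes their baseline proportions equal. A recipient with a larger donor-reactive repertoire on day 0 can show a higher proportion later without any expansion, and may also be more likely to reject. A significant t-test could then mean that rejectors started higher rather than that their clones expanded. The reverse error is also possible: real expansion from a lower baseline could be missed.

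The two explanations lead to different uses. A higher starting level points to risk marking before transplantation. Expansion is what the study hopes to see ahead of graft damage.

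**Working it through.** **Inputs.** From the power statement: 15 per group, SD 0.1 in each, difference 0.106, power 80%. Alpha and sidedness are not stated, so two-sided 0.05 is assumed. Three further inputs are not in the documents and are assumed: the baseline gap g between the groups (0 to 0.106), the pre/post correlation r (0 to 0.9), and a baseline SD of 0.1, equal to the post-transplant SD.

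**1. The plan's own figure.** For a two-sample t-test with 28 df, the noncentrality is 0.106 / (0.1 × √(2/15)) = 0.106 / 0.03651 = 2.903 and the critical value is 2.048. Power is 80.0%. The figure of 0.106 reproduces, for a post-transplant level.

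**2. The stated test when nothing changes.** Suppose neither group expands or contracts on average and a baseline gap g carries forward in full. The post-transplant means then differ by g, and the noncentrality is g / 0.03651.

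| g | noncentrality | probability of significance |
|---|---|---|
| 0 | 0 | 5% |
| 0.025 | 0.685 | 10% |
| 0.05 | 1.369 | 26% |
| 0.075 | 2.054 | 51% |
| 0.10 | 2.739 | 75% |
| 0.106 | 2.903 | 80% |

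In a simulation of the same situation (20,000 runs per setting; g = 0, 0.05 and 0.10; r = 0.5, 0.7 and 0.9), a t-test on within-patient change was significant in about 5% of runs throughout.

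**3. Baseline adjustment (ANCOVA) in the same situation.** The pooled slope is about r when the two SDs are equal, so adjustment removes r × g and leaves (1 − r) × g. At g = 0.05 and r = 0.7, 0.015 remains. Simulated false-positive rates (20,000 runs) for r = 0.3, 0.5 and 0.7 are about 15%, 11% and 8% at g = 0.05, and about 40%, 27% and 17% at g = 0.10. This is better than the level test but not clean.

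**4. Power at 0.106 with no baseline gap, raw scale.** The SD of the change is 0.1 × √(2(1 − r)). The adjusted SD is about 0.1 × √(1 − r²), ignoring the one df lost.

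| r | SD of change | power, change | adjusted SD | power, ANCOVA |
|---|---|---|---|---|
| 0 | 0.141 | 51% | 0.100 | 80% |
| 0.3 | 0.118 | 66% | 0.095 | 84% |
| 0.5 | 0.100 | 80% | 0.087 | 90% |
| 0.7 | 0.077 | 95% | 0.071 | 97% |
| 0.9 | 0.045 | >99% | 0.044 | >99% |

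The change score matches the level test at r = 0.5, gains above it and loses below it. None of these figures applies to a log ratio, because the documents give no effect size or SD on that scale.

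**The case against.** The strongest reply is that the t-test is a proper test of what it names. The abstract and Methods/design also frame the study as a comparison of repertoires between rejectors and non-rejectors at biopsy, and a level that separates them at a time-matched for-cause biopsy is a legitimate target. That stands. The objection is to calling such a difference expansion or deletion, not to the test itself.

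A reader might infer three stronger criticisms that the documents do not support.

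- **That the plan leaves open which post-transplant sample is tested.** The wording in Statistical methods is loose. But Methods/design specifies the rejection episode against time-matched for-cause biopsies, and the power statement counts 15 samples per group, the same number as the patients. Together these point to the index-biopsy sample.
- **That baseline data are ignored altogether.** The abstract, Outcome parameters and Discussion all foresee looking at change over time, and an article may leave the details of those analyses to a fuller plan. What is fixed in the text, and does not fit the outcome, is the one named test and its power statement.
- **That a false claim of expansion is likely.** Neither g nor r is given. The 75% case assumes a gap of 0.10, nearly the whole target effect, carried forward unchanged. The figures show that the error can occur, not how large it will be.

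It is also fair to say that change from baseline has a price, since it is less powerful than the level test when r is below 0.5. A baseline-adjusted sensitivity analysis does not rescue a primary test with too little power.

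**Conclusion.** The mismatch holds. The outcome is a change, while the only named test and the power statement concern a level, in groups whose baselines nothing equalises. The power arithmetic itself is right. With no change in either group, a persisting gap of 0.025, 0.05 or 0.10 would make the stated test significant in about 10%, 26% or 75% of trials, against about 5% for within-patient change. This rests on two-sided 0.05, SD 0.1 at both times and a gap carried forward in full; the last is purely an assumption. The point should be fixed, because a positive result from the test as written would not answer the question in Outcome parameters. It does not make the comparison of levels invalid.

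**What to change.** In Statistical methods, compare rejectors and non-rejectors on a baseline-referenced measure: the within-patient change in the proportion of MLR-defined clones from the day-0 unstimulated sample to the index-biopsy sample. Choose the raw difference or the log ratio in advance. Report the post-transplant level and an ANCOVA alongside, and note that ANCOVA removes a baseline gap only in part.

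Restate the power under Sample collection, and Fig. 2, for the chosen measure over a range of pre/post correlations. On the raw scale the change-score figures in the second table above can serve. A log ratio needs its own assumed effect size and SD.

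No new samples or sequencing are needed. The costs are the restated power, which is less favourable than 80% if r is below 0.5, and, for a log ratio, a pre-set offset for zeros.

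If the level test stays as the only test, Outcome parameters should describe the outcome as a post-transplant level, and no claim of expansion or deletion should rest on it.

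### Controls are time-matched to rejection cases, but the planned t-test and its power statement ignore time since transplantation, which costs precision without inflating error

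*Protocol article*

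**What the plan says.** Three places in the protocol article bear on this.

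- **Design (Methods/design).** "Fifteen patients with histological proven acute T cell mediated rejection will be compared" with "15 patients without histopathological signs of alloimmune response in time matched for-cause biopsies". The article does not say whether each control is tied to one case or whether controls come from a common time window. It gives no reason for the matching.
- **Analysis (Statistical methods).** The section is one sentence: the proportion of alloreactive clones after transplantation in "rejectors and non-rejectors will be compared by means of t-test". It names no pairing, matched set or time term, and does not say which form of t-test is meant.
- **Power (text after the Fig. 1 legend, under Sample collection).** "Including 15 samples per group (Rejectors, non-rejectors"), the study is said to have "80% power to detect a minimum difference of 0.106", for "patients from the two groups assuming a standard deviation of 0.1 each". Significance level, sidedness and any correlation between matched patients are not given.

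**The concern.** The design controls time since transplantation, while the analysis and its power statement treat the 30 values as unrelated. For-cause biopsies have no fixed date, so this time can vary widely between patients. The article itself gives grounds for thinking that it matters: it plans to study repertoire diversity over time, and its Discussion cites a study in which donor-reactive clones declined after transplantation in tolerant patients.

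When groups are balanced on a variable that predicts the outcome, the difference in means varies less than the unpaired formula assumes. The computed standard error is then too large, the confidence interval too wide and the p-value too big. With 15 cases in the study's only named comparison, a real difference could be missed for want of precision that the design already provides.

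**Working it through.** **Inputs.** From the article: 15 per group, SD 0.1 in each group, 80% power, difference 0.106. Assumed: two-sided 5% level, because it reproduces the stated figure (one-sided 5% would give 88.2% power). Also assumed: the share r of outcome variance explained by time since transplantation, over the range 0 to 0.5. With close time matching, r is also the correlation between matched values.

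**Step 1: reproduce 0.106.** The unpaired standard error is 0.1 × √(2/15) = 0.03651. The noncentrality needed for 80% power with 28 degrees of freedom is 2.902. The detectable difference is 2.902 × 0.03651 = 0.10598, and power at 0.106 is 80.0%. The figure therefore follows from an unpaired test with no further input.

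A paired calculation (14 degrees of freedom, noncentrality 3.013) gives 3.013 × 0.03651 × √(1 − r). This equals 0.106 only at r = 1 − (2.902/3.013)² ≈ 0.07, a value that the article nowhere mentions. If 0.1 were the SD of pair differences, 15 pairs would detect 0.078. The power statement is thus unpaired in substance.

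**Step 2: the unpaired test when time matters.** The true standard error of the difference is 0.03651 × √(1 − r), but the test uses about 0.03651. It is therefore too large by 1/√(1 − r): 1.05 at r = 0.1, 1.12 at 0.2, 1.20 at 0.3 and 1.41 at 0.5. Type I error and power of the unpaired test come from 100,000 simulated studies per setting, with normal data and exact matching.

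**Step 3: the alternatives.** A linear model with one time covariate has 27 degrees of freedom (noncentrality 2.906), so its detectable difference is 2.906 × 0.03651 × √(1 − r). Paired figures use the formula in step 1.

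| r | Unpaired: true error | Unpaired: power at 0.106 | Covariate: power at 0.106 | Covariate: detectable | Paired: power at 0.106 | Paired: detectable |
|---|---|---|---|---|---|---|
| 0 | 5.0% | 80.1% | 79.9% | 0.106 | 77.0% | 0.110 |
| 0.1 | 4.0% | 81.2% | 83.9% | 0.101 | 81.2% | 0.104 |
| 0.2 | 3.0% | 82.4% | 87.9% | 0.095 | 85.5% | 0.098 |
| 0.3 | 2.2% | 83.8% | 91.7% | 0.089 | 89.7% | 0.092 |
| 0.5 | 0.8% | 87.3% | 97.7% | 0.075 | 96.8% | 0.078 |

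The covariate columns assume that the time effect is linear on the chosen scale, has the same slope in both groups, and that the groups are balanced on time. With looser matching, the unpaired test would be less conservative than shown.

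**Reading the table.** The covariate model gives up almost nothing when time is irrelevant (79.9% against 80.1%) and gains at every positive r shown. The paired test is weaker than the unpaired test at r = 0 and level with it at about 0.1.

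**The case against.** Several objections are fair.

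- **The text is short of detail.** The article does not use the term independent-samples, and a paired t-test is also a t-test. An unpaired power calculation is a usual choice when no correlation is known and does not by itself fix the final test. A full protocol or SAP may say more. This stands as a limit: the unpaired reading is an inference, though a strong one. The point remains because the article itself names the test and sizes the study on it, and neither uses the matching that it also states.
- **No pairs are described.** A reader might infer that each control is matched to one case and that a paired test is therefore required. The article does not support this, since its wording fits window matching equally well, and then there are no pairs to analyse.
- **The size of the time effect is unknown.** Each recipient's clones are defined against that recipient's own donor, so large variation between persons is plausible. The cited study also suggests that the time course may differ between rejecting and non-rejecting patients, which would weaken the correlation. Both points stand, which is why the range starts at zero.
- **The error is in the safe direction.** A reader might infer that the test is invalid or the study underpowered. Neither follows. For any r of zero or more, type I error stays at or below nominal and power at 0.106 does not fall below the stated 80%.
- **The matching is not wasted.** A reader might infer that an unpaired analysis discards it. It does not: balance on time still protects the difference in means against confounding by time. Only precision is forgone.

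**Conclusion.** The point holds as a loss of precision of minor to moderate size. The planned analysis, as far as the article states it, leaves out the variable on which controls were matched. If time explains 10% to 20% of the variance, the unpaired test runs at a true error of about 4% to 3% instead of 5%. Adjusting for time would lower the detectable difference from 0.106 to about 0.101 to 0.095 with the same patients. If time explains nothing, nothing is lost under the present plan.

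The conclusion rests on three assumptions: a two-sided 5% level, an unpaired final test as the power statement implies, and a non-negative association between time since transplantation and the outcome. The documents do not fix the strength of that association, so confidence is good that design and analysis do not fit together, and low on how much precision is at stake.

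**What to change.** 1. State in Methods/design whether controls are matched individually 1:1 or by time window.
2. In Statistical methods, replace the bare t-test by a linear model for the proportion of alloreactive clones, with group and time since transplantation (for example, log days) as terms. This is suitable under either form of matching. Use a paired or matched-set analysis only if controls are individually matched 1:1.
3. Keep 0.106 as the conservative unadjusted figure. Add the adjusted detectable difference over a range of explained variance (about 0.106, 0.101 and 0.095 at 0, 0.1 and 0.2), and state the significance level and sidedness.

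The cost is wording and one degree of freedom, with no new patients, samples or assays. A paired test would cost more: it falls to 77% power at 0.106 if the within-pair correlation is zero, and it loses a whole pair whenever one member's sample fails.
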